### Secondary Outcome Measures

Secondary endpoints include the difference in the OSTQOL score between depot and control group at month 12 (t_4_), comparisons between the depot and control group in patient satisfaction (Client Satisfaction Questionnaire–CSQ-8) at month 12 (t_4_), substance use (i.e., on the basis of self-reporting) at month 6 (t_3_) and month 12 (t_4_), the retention rate in treatment at month 12 (t_4_), psychological distress (Brief Symptom Inventory 18) at t_4_, social participation at month 6 (t_3_) and month 12 (t_4_) as well as the cost-effectiveness (on the basis of quality-adjusted life years (QALYs); EuroQOL five dimensions questionnaire (EQ-5D) at month 12 (t_4_). Three secondary endpoints will be measured solely in the depot group, the acceptance of the depot medication and its application measured by the Treatment Satisfaction Questionnaire for Medication (TSQM-14) at month 1, 3, 6 and 12 (t_1_-t_4_), the dosage adequacy measured by the Opiate Dosage Adequacy Scale (ODAS) at month 1, 3, 6 and 12 (t_1_-t_4_) and changes in quality of life domains (OSTQOL subscales) in depot group over time between baseline (t_0_) and month 12 (t_4_). Possible adverse reactions will be assessed by a physician and recorded as part of the documentation of adverse events (AEs) and adverse drug reactions (ADRs). An overview of all primary and secondary outcome measures is provided in Table 1.

**Table 1 T1:** Overview of primary and secondary outcome measures.

**Primary outcome measure**	**Difference of OSTQOL total score in depot group between baseline (t_0_) and month 12 (t_4_)**
**Secondary outcome measures**	1. Quality of life (OSTQOL score) between depot and control group at t_4_ 2. Acceptance (TSQM-14) of injectable depot buprenorphine between t_1_ and t_4_ 3. Patient satisfaction with OST care (CSQ-8) between depot and control group at t_1_- t_4_ 4. Dosage adequacy (ODAS) in depot group at t_1_-t_4_ 5. Substance use (i.e., self-reporting) between depot and control group at t_3_ and t_4_ 6. Psychological distress (BSI-18) between depot and control group at t_4_ 7. Social participation between depot and control group at t_4_ 8. Retention rate (percentage of patients) in depot group at t_3_ and t_4_ 9. Cost-effectiveness [on the basis of quality-adjusted life years (QALYs); EQ-5D] between depot and control group at t_4_ 10. Changes in quality of life domains (OSTQOL subscales) in depot group between baseline (t_0_) and month 12 (t_4_)

*t_0_, baseline; t_1_, month 1; t_2_, month 3, t_3_, month 6 and t_4_, month 12; OSTQOL, Opioid Substitution Treatment Quality of Life scale; TSQM-14, Treatment Satisfaction Questionnaire for Medication; CSQ-8, Client Satisfaction Questionnaire; ODAS, Opiate Dosage Adequacy Scale; EuropASI, European Addiction Severity Index; BSI-18, Brief Symptom Inventory 18; CRF = Case-Report Form; EQ-5D, EuroQOL five dimensions questionnaire*.

### Variables

The following variables will be collected at baseline (t_0_) and follow-ups [month 1 (t_1_), 3 (t_2_), 6 (t_3_), 12 (t_4_)]:

- **Sociodemographic data** including gender, age, current housing, work, family status/partnership.- **Health data** will be collected using the Opiate Treatment Index-Health Symptom Scale (OTI-HSS), a symptom checklist to assess the patient's current health status with regard to medical problems that opioid users often develop (e.g., injection-related problems, cardio/respiratory problems, musculoskeletal problems, neurological problems, gastro-intestinal problems (21, 22).- **OST data** (medication, doses) routinely collected by the OST practice/clinic.- **Quality of life** will be measured by the OSTQOL, a disease-specific instrument for measuring quality of life among patients in OST (20). First analyses in developmental processes of the OSTQOL showed acceptable internal consistencies of all subscales (personal development, psychological stress, social contacts, material well-being, OST and discrimination), with Cronbach's alpha between 0.75 and 0.88, as well as a good convergent and discriminant validity of the instrument (20).- The **patient acceptance** of injectable depot buprenorphine will be measured along the four key dimensions of the Treatment Satisfaction Questionnaire for Medication (TSQM-14) (effectiveness; side effects; convenience and global satisfaction).- The **Client Satisfaction Questionnaire (CSQ-8)** will be used to measure the patients' satisfaction with the overall OST care. The short 8-item instrument has been frequently used in substance use research including OST (23, 24) and has shown a high internal consistency and concurrent validity (25).- Parts (heroin craving, acceptance of the OST medication) of the **Opiate Dosage Adequacy Scale (ODAS)** will be used to measure the adequacy of opioid doses among the patients in the depot buprenorphine group. The ODAS consists of six domains (heroin consumption, narcotic blockade, mental and somatic opiate withdrawal syndrome, craving for heroin, and OST overdosing) including items which can be answered by the patient. Scores range between 1 (worst) and 5 (best). Cut-off scores of 3 or less in any ODAS domain will be regarded as not adequately dosed. The ODAS was found to have a good validity and reliability to measure and assess buprenorphine dose adequacy in the context of OST (26).- Data on **substance use** will be collected on the basis of patient self-report using the drug and alcohol use domain of the European Addiction Severity Index (EuropASI) (27). The data on substance use will be complemented by urine samples collected within routine OST care. The urine samples will be tested for heroin, non-prescribed substitutes, cocaine/crack, amphetamine, cannabis and benzodiazepine use.- **The psychological distress** among the patients will be measured by the Brief-Symptom-Inventory 18 (BSI-18), (28). The questionnaire comprises 18 items on physical and psychological symptoms, rated on a 5-point Likert scale (0 = not at all; 4 = very much) with regard to the last 7 days, and yields 3 sub-scores for depression, anxiety, and somatization, as well as an overall Global Severity Index (GSI).- **Social participation** will be measured by a self-developed short questionnaire including questions on the number and kind of social activities (e.g., recreational or physical activities, activities with friends, family) within the last week.- Data to calculate the **retention in treatment** will be collected by the date of ending OST or changing OST medication. The dates will be collected retrospectively by the treatment staff at any follow-up timepoint of the study. Retention in treatment will be calculated by dividing the number of patients in each study arm at each follow-up visit by the total number of patients in each study arm at baseline.- Quality-adjusted life years (QALYs) will be used for the **cost-effectiveness analysis**. Respective data will be collected with the EuroQOL five dimensions questionnaire (EQ-5D) (29).

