#### Secondary Outcome Analyses

Secondary data analyses will be carried out in accordance with the scale levels of the variables or scores and indices (drug consumption, somatic or mental health symptoms, quality of life, withdrawal symptoms, craving, treatment satisfaction) and along the expected relationships between individual variables, e.g., in the context of bivariate or multivariate analyses. Comparisons between depot patients and matched control group will be done by a mixed model approach with baseline OSTQOL score and the (pairwise) cluster term as covariates and will include all follow-up measurement points, such as month 3 and month 6 (see Table 2). Retention rates will be analyzed using descriptive statistics. For group comparisons, Chi^2^-tests (percentages) as well as Kaplan-Meier survival methods and Log-Rank Tests will be used. The significance level will be defined at *p* < 5%.

**Table 2 T2:** Overview of outcome domains, instruments and measurement.

**Outcome domain**	**Instrument**	**t_**0**_**	**t_**1**_**	**t_**2**_**	**t_**3**_**	**t_**4**_**
Quality of life	OSTQOL	x		x	x	x
Acceptance	TSQM-14	x	x	x	x	x
Patient satisfaction with	CSQ-8	x	x	x	x	x
OST care						
Dosage adequacy	ODAS	x	x	x	x	x
Substance use	EuropASI, Urine samples	x	x	x	x	x
Psychological distress	BSI-18	x			x	x
Social participation	Self-constructed questionnaire	x			x	x
Retention	CRF		x	x	x	x
Cost-effectiveness	EQ-5D	x			x	x
Health	OTI-HSS	x			x	x
Adverse events	AE, SAE, ADR	If necessary				

*t_0_, baseline; t_1_, month 1; t_2_, month 3, t_3_, month 6 and t_4_, month 12; OSTQOL, Opioid Substitution Treatment Quality of Life scale; TSQM-14, Treatment Satisfaction Questionnaire for Medication; CSQ-8, Client Satisfaction Questionnaire; ODAS, Opiate Dosage Adequacy Scale; EuropASI, European Addiction Severity Index; BSI-18, Brief Symptom Inventory 18; CRF = Case-Report Form; EQ-5D, EuroQOL five dimensions questionnaire; OTI-HSS, Opiate Treatment Index-Health Symptom Scale; AE, adverse event; SAE, serious adverse event; ADR, adverse drug reaction*.

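### The dosage-adequacy endpoint applies an any-domain ODAS cut-off to two selected parts, only one of them a listed domain, so the result is not ODAS dosage adequacy

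*Protocol article*

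**What the plan says.** The ODAS entry in the Variables section of the protocol article makes five statements:

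- **What is administered.** "Parts (heroin craving, acceptance of the OST medication) of the" ODAS are to measure whether opioid doses in the depot group are adequate.
- **What the scale contains.** "The ODAS consists of six domains (heroin consumption, narcotic blockade, mental and somatic opiate withdrawal syndrome, craving for heroin, and OST overdosing".
- **How it is scored.** "Scores range between 1 (worst) and 5 (best".
- **How patients are classified.** "Cut-off scores of 3 or less in any ODAS domain will be regarded as not adequately dosed".
- **What supports it.** "The ODAS was found to have a good validity and reliability to measure and assess buprenorphine dose adequacy in the context of OST".

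The Secondary Outcome Measures section names the endpoint as "the dosage adequacy measured by the Opiate Dosage Adequacy Scale (ODAS) at month 1, 3, 6 and 12", for the depot group only. Table 1 (item 4) and Table 2 also label it dosage adequacy (ODAS). None of these three places says that the scale is given in part.

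**The concern.** The rule and the validity statement are written for a scale with six domains, but the data come from two parts, one of which is not on the domain list. Five listed domains are not among the administered parts: heroin consumption, narcotic blockade, mental withdrawal, somatic withdrawal and overdosing. A patient who would fail only in one of these cannot be identified by a domain cut-off applied to what is collected with the ODAS.

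What is at stake is the meaning of one named secondary endpoint. A reader of the results would take the percentage adequately dosed at months 1, 3, 6 and 12 as the outcome of the validated instrument. It would instead rest on craving alone, or on craving plus an item outside the listed domains.

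**Working it through.** The documents state no adequacy rate, sample size or power for this endpoint, so there is no figure to reproduce. The check is one of logic, followed by an illustration of size.

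**1. Match the parts to the domains.** Counting mental and somatic withdrawal separately, the list gives the stated six.

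| Listed ODAS domain | Among the administered parts? |
|---|---|
| Heroin consumption | no |
| Narcotic blockade | no |
| Mental withdrawal | no |
| Somatic withdrawal | no |
| Craving for heroin | yes |
| Overdosing | no |

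Acceptance of the medication is administered but is not on the list. One of six domains can be scored.

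**2. Direction if only listed domains count.** A patient is adequate on the full scale only if all six domains score above 3. Everyone who passes all six also passes craving, so P(adequate on craving) ≥ P(adequate on all six). The inequality is strict as soon as one patient fails only in an omitted domain.

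**3. Illustrated size.** The failure rate per domain, q, and the correlation between domains are assumptions; the documents give neither. With independent domains, the share adequate is 1 − q on craving and (1 − q)^6 on all six. Correlated domains were simulated with equicorrelated normal latent variables (500,000 draws).

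| Assumed q | Craving alone | Six domains, independent | Correlation 0.3 | Correlation 0.6 | Correlation 0.9 |
|---|---|---|---|---|---|
| 5% | 95% | 0.95^6 = 73.5% | 78.0% | 83.3% | 90.0% |
| 10% | 90% | 0.90^6 = 53.1% | 61.9% | 70.9% | 81.8% |
| 20% | 80% | 0.80^6 = 26.2% | 39.4% | 52.2% | 67.5% |

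The excess runs from 95 − 90.0 = 5.0 points to 80 − 26.2 = 53.8 points.

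**4. Direction if acceptance is also scored as a failing criterion.** Let a be the assumed share failing on acceptance, independent of the domains. The share adequate on the two parts is then (1 − q)(1 − a).

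- q = 5%, a = 10%: 0.95 × 0.90 = 85.5%, above the 73.5% on six domains.
- q = 5%, a = 30%: 0.95 × 0.70 = 66.5%, below 73.5%.

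The sign therefore depends on how acceptance is scored and how often patients fail it, and the article states neither.

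**The case against.** Several objections have force.

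- **The rule may mean any domain administered.** The cut-off sentence does not contain the word six. On this reading the rule is a cut-off on craving, perhaps with acceptance, and can be carried out. The result is still not what the endpoint's name promises, and the cited validity is stated for the ODAS and not for the two parts.
- **A journal article condenses.** A fuller document might say how the parts are scored. But the article itself states the parts, the domains, the cut-off and the validity claim, and these do not fit together. That is more than a detail left out.
- **Overstatement is not certain.** A reader might infer that adequacy will necessarily be reported too favourably. This follows only if acceptance is not a failing criterion (step 4). The percentages in step 3 compare craving alone with six domains under assumed rates, so they show how wide the possible range is and estimate nothing.
- **Safety does not rest on this endpoint.** A reader might infer that under- or overdosing would go unseen in the study. The documents do not support that. Heroin use is recorded by EuropASI and urine samples at every visit (Table 2). Medical staff document adverse events, and life-threatening overdose is the article's own example of a serious one. The TSQM-14 covers effectiveness and side effects, and the OTI-HSS covers health symptoms. No passage says these sources feed the ODAS classification, so they do not repair the label.
- **Withdrawal symptoms in the analysis section.** Secondary Outcome Analyses lists "somatic or mental health symptoms, quality of life, withdrawal symptoms, craving, treatment satisfaction" among the variables to analyse. A reader might see a contradiction with the omitted withdrawal domains. The list does not attribute withdrawal to the ODAS, and the case-report forms, which include routine clinical data and provider and patient questionnaires, are not reproduced. No change to that list is warranted.
- **The endpoint is minor.** It is one of ten secondary outcomes in Table 1 and is confined to the depot group. This limits the weight of the point but does not remove it.

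**Conclusion.** The point holds as a mismatch between what is measured and what is claimed. Two ODAS parts, one of them outside the listed domains, cannot yield the any-domain classification of a six-domain scale or carry the validity cited for that scale.

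The direction of the error is conditional. If only listed domains count, the adequate share is never below the full-scale share, and it is higher when any patient fails only in an omitted domain. If acceptance also counts, the share may be too high or too low. The size cannot be derived from the documents; the 5 to 54 points rest wholly on assumed failure rates of 5% to 20% per domain, correlations of 0 to 0.9, and scoring of craving alone.

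The primary endpoint and the comparisons between the depot and control groups do not use this classification, and adverse-event reporting is separate. The point concerns measurement and labelling only and makes no statement on dosing. It should be corrected because the change is cheap and alters what secondary endpoint 4 can conclude.

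**What to change.** Rename secondary endpoint 4 as heroin craving and medication acceptance (selected ODAS parts) in Secondary Outcome Measures, Table 1 and Table 2. In Variables, report the scores of the two parts, remove the classification as adequately or not adequately dosed, and remove the validity sentence or state plainly that it concerns the ODAS as such and not the selected parts. Keep the classification only if all six domains are in fact collected; in that case correct the sentence that says only parts are used.

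The renaming costs wording only, and the endpoint then supports a narrower conclusion. Adding the missing domains now is not clearly cheap. Recruitment began in April 2020, so completed visits could lack them, and the article does not establish that every domain can be answered by the patient.

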### Selection and Treatment of Participants

Inclusion and exclusion criteria are listed below. Patients who are not eligible for the treatment with injectable subcutaneous depot buprenorphine according to Summary of Product Characteristics (SmPC) will be excluded from the depot buprenorphine arm, but can be part of the control group, if pairwise matching criteria apply. If a patient drops out from treatment with injectable depot buprenorphine (and returns to previous medication or give up OST at all) he or she should be followed up for the whole study period (unless he/she withdraw the study consent).

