### Assessment and Timelines

All data will be collected in case-report-forms (CRFs) including documentation sheets for clinical routine data and questionnaires for OST providers and patients. After baseline (t_0_), follow-up assessments will be made on month 1 (t_1_), month 3 (t_2_), month 6 (t_3_), and month 12 (t_4_). For the case that OST ends prematurely (before the end of the 12-month study period), study participation continues, and the patient will be asked to take part in the remaining follow-up assessments. All patients will receive reimbursements of € 10,-for each assessment.

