#### Primary Outcome Analysis

The main analysis will be carried out according to the intention-to-treat principle (ITT), considering all patients who have started the substitution treatment with injectable depot buprenorphine. The primary outcome measure is the difference of OSTQOL (20) scores between baseline (t_0_) and month 12 (t_4_) in the depot group. The average OSTQOL mean score will be compared between these time points and analyzed for statistical significance using dependent *t*-tests. It is tested against the statistical null hypothesis (H0) of a decrease or no change in the OSTQOL mean score. The alternative hypothesis (H1) consists in a significant improvement of the OSTQOL mean score, which corresponds to an improvement in quality of life of the patients.

H0: M (Month 12) ≤ M (baseline) (OSTQOL mean score at 12 months ≤ baseline OSTQOL mean score)H1: M (Month 12) > M (baseline) (OSTQOL mean score at 12 months > baseline OSTQOL mean score).

The hypothesis will be tested two-sided at a significance level of *p* < 5%. The statistical analyses will be made according to the intention-to-treat (ITT) as well as to the per-protocol (PP) principle. The PP sample is defined by all patients who have undergone OST with injectable subcutaneous depot buprenorphine for at least 12 months and for whom sufficient baseline and 12-month data are available. The ITT sample comprises all patients who provided a written consent, who have undergone the baseline assessment, and–for patients in the depot study arm–who have received the first dose of injectable depot buprenorphine. For the ITT analysis, data from all study patients will be used independently of their status in or out of treatment with injectable depot buprenorphine. Missing values at the 12-month time point will be replaced by missing imputation procedures. These may either include last observation carried forward (LOCF) approaches or longitudinal mixed model analyses using all available follow-up assessments. The choice of imputation procedures for the ITT analysis will depend on the proportion of missing values at the 12-month time point as well as the quantity of available data at 3-month and 6-month follow-up, and will be determined by sensitivity analyses.

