### Drop-Outs

Patients who cannot be analyzed (i.e., missing baseline and follow-up data, not starting treatment with injectable depot buprenorphine) will be excluded from the data analyses. If either the medication with injectable depot buprenorphine or OST treatment or study participation (or both) is discontinued, the reason for the termination or circumstance will be documented. Patients who change from the depot group to the control group or vice versa will be followed-up as long they withdraw their study participation or terminate OST (drop-out). In both cases the reasons will be documented. A drop-out analysis will be performed to determine potential drop-out criteria.

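### The stated retention formula has no still-on-treatment condition, so treatment leavers who remain in follow-up count as retained

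*Protocol article*

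**What the plan says.** Under Variables, the data for retention in treatment "will be collected by the date of ending OST or changing OST medication", and treatment staff record these dates retrospectively at follow-up. The same bullet then defines the rate as "dividing the number of patients in each study arm at each follow-up visit by the total number of patients in each study arm" at baseline.

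Three other places keep patients in the study after they leave treatment:

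- Selection and Treatment of Participants, on a patient who stops depot buprenorphine or gives up OST: "he or she should be followed up for the whole study period", unless consent is withdrawn.
- Assessment and Timelines, on OST that ends early, without limitation to one arm: "study participation continues, and the patient will be asked to take part in the remaining follow-up assessments".
- Primary Outcome Analysis, on the ITT analysis: "data from all study patients will be used independently of their status in or out of treatment with injectable depot buprenorphine".

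Drop-Outs adds a rule for switchers: "Patients who change from the depot group to the control group or vice versa will be followed-up". For these patients, however, it labels termination of OST a drop-out.

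Secondary Outcome Analyses plans descriptive retention rates and chi-square tests on percentages for group comparisons, and says that "Kaplan-Meier survival methods and Log-Rank Tests will be used". Table 1 lists the retention rate for the depot group at months 6 and 12.

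**The concern.** Secondary Outcome Measures names retention in treatment as an endpoint. The formula counts members of the study arm at a visit, and being in the study is not the same as being in treatment when leavers are deliberately followed. A leaver who is still followed adds to the numerator. If presence is judged by the visit, a treated patient who misses it is subtracted. The better the study holds on to its leavers, the less the figure says about treatment.

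Taking membership of the arm to mean current medication does not rescue the formula. A patient who moves from depot to another OST medication could then enter the control numerator without being in the control denominator.

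At stake are the reported retention percentages and the chi-square comparison. There is also a risk that the percentages and the Kaplan-Meier curves show two different retention figures for one endpoint.

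**Working it through.** **The plan's own figures.** The protocol states no expected retention rate, so there is none to reproduce. The depot sample size can be checked: 128 evaluable patients and 40% drop-out give 128 / 0.6 = 213.3, in line with the stated 213. It does not depend on the retention definition.

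**Formula as written.** Let r be the true share still on the arm's treatment, a the share of on-treatment patients present at the visit, and f the share of leavers present. Then

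formula value = r·a + (1 − r)·f

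It equals r for every r only if a = 1 and f = 0, that is, if every leaver is lost and everyone else attends. It overstates r when (1 − r)·f exceeds r·(1 − a). All values of r, a and f below are assumptions.

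| r | a = 1, f = 1 | a = 0.95, f = 0.80 | a = 0.90, f = 0.50 | a = 1, f = 0 |
|---|---|---|---|---|
| 0.5 | 100% | 87.5% | 70% | 50% |
| 0.6 | 100% | 89% | 74% | 60% |
| 0.8 | 100% | 92% | 82% | 80% |
| 0.9 | 100% | 93.5% | 86% | 90% |

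Overstatement is the usual result in this table. The exception is r = 0.9 with a = 0.90 and f = 0.50, where missed visits outweigh followed leavers and the formula falls below the truth.

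**Comparison, same attendance in both arms.** True retention 60% versus 80%, a = 0.9, f = 0.5:

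- 0.6·0.9 + 0.4·0.5 = 0.74
- 0.8·0.9 + 0.2·0.5 = 0.82

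The gap is multiplied by a − f = 0.4, so 20 points become 8. With f = 0.3 the gap is 12 points; with f = 0.7 it is 4.

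**Effect on the test.** For true 60% versus 75% with 213 per arm, a two-sided 5% comparison of proportions has 91% power. With a = 1 and f = 0.8 the formula shows 0.6 + 0.4·0.8 = 92% versus 0.75 + 0.25·0.8 = 95%, and power is 24%.

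**Comparison, attendance differing by arm.** True retention 80% in both arms, with (a, f) of (0.9, 0.5) in one and (0.8, 0.4) in the other:

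- 0.8·0.9 + 0.2·0.5 = 0.82
- 0.8·0.8 + 0.2·0.4 = 0.72

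A 10-point difference appears where none exists.

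**Drop-Outs reading.** Suppose those who end OST are lost and switchers are kept. With 20% of depot patients switching and 20% ending OST, true depot retention is 100% − 20% − 20% = 60%, but the formula gives 80%.

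**Current-medication reading.** If 20% of 213 depot patients move to TAU and are counted there, a true control retention of 80% becomes (0.8·213 + 0.2·213) / 213 = 100%. A true 90% becomes 110%.

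**The case against.** The strongest reply is that the bullet should be read as a whole. It opens with the end and change dates, which would be pointless if retention were a head count at visits. On that reading the visit only names a time point, and the numerator means patients still in their arm's treatment according to those dates. That is probably the intent, and nothing in the text says outright that a missed visit counts as loss. But the sentence that gives the calculation does not use the dates or mention treatment status. If intent and formula differ, the formula has to change.

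Three stronger conclusions that a reader might draw are not supported:

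- **That both arms will show about 100%.** This needs complete follow-up. Sample Size Calculation expects 40% drop-out by month 12, without saying whether from study or treatment, and Drop-Outs treats ending OST as drop-out for switchers. If 40% left the study regardless of treatment status, the formula would give about 60% in both arms, which is still attendance rather than retention.
- **That any true difference shrinks towards zero.** This holds when attendance patterns are similar in the two arms. When they differ, a gap can be created.
- **That the whole retention analysis fails.** Kaplan-Meier and log-rank can run on the recorded dates and need not inherit the problem. Table 1 also lists retention for the depot group only, so that item contains no between-arm gap; the comparison arises in Secondary Outcome Analyses.

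The current-medication reading is likewise only a possibility. Drop-Outs says that switchers are followed, not that they are recounted in the other arm.

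**Conclusion.** The point holds as a defect in a stated rule for a secondary endpoint. As worded, the formula does not measure retention in treatment, because followed-up leavers count as retained. It generally overstates retention when many leavers are followed and few treated patients miss visits. Its size cannot be fixed from the protocol. In the illustration, 60% versus 80% is reported as 74% versus 82%, which rests on assumed retention and on assumed attendance that is equal in both arms. The direction of bias in the group comparison is not determined in general.

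The retention percentages and the chi-square test are affected. The time-to-event analyses, the primary endpoint and the sample size are not. It should be fixed before analysis.

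**What to change.** Replace the formula sentence in Variables so that:

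1. A patient is retained at month k if treatment records show no end of OST and no change from the arm's medication on or before month k, whether or not the study visit took place. Patients with no recorded end or change date who are known to be in treatment are then classified as retained.
2. Each patient stays in the baseline arm in both numerator and denominator.
3. Patients lost with unknown treatment status have a stated rule. One option is to censor them at the last known treatment date in Kaplan-Meier and count them as not retained in the percentages, with a sensitivity analysis.
4. This one variable serves the percentages, the chi-square test and Kaplan-Meier.
5. Visit attendance is reported separately, as completeness of follow-up.

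Drop-Outs must also be reconciled with Selection and Treatment of Participants and with Assessment and Timelines on follow-up after OST ends.

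The cost is a few sentences. Treatment staff already collect the dates, and neither the sample size nor the visit schedule changes.
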